#### Verum Acupuncture

The treatment plan for acupuncture is dependent on the Acupuncture Therapeutics textbook (21) and the clinical experience of acupuncture experts. Subjects randomized to the verum acupuncture group will receive 24 sessions of acupuncture treatment (3 times a week for 8 weeks; 30 min every session). Baihui (GV20), Yintang (GV29), Shenmen (HT7), Taichong (LR3), Tianshu (ST25), and Zusanli (ST36) will be used in the verum acupuncture group. Acupuncturists will use sterile needles (Huatuo disposable acupuncture needle) 0.30 × 40 mm in size in the acupoints, twirling and lifting will apply for 30 s at each acupoint to achieve the typical acupuncture sensation of Deqi (soreness, numbness, distension, and heaviness), and needles will be retained in place for 30 min.

#### Minimal Acupuncture

Non-acupoints (Table 1) without antidepressant therapy will be used to provide acupuncture for subjects in the minimal acupuncture group. Acupuncturists will use sterile needles 0.30 × 25 mm in size punctured 2 mm in depth without achieving a Deqi sensation (feel nothing after the needle is punctured). The course of treatment will be the same as that of the verum acupuncture group. After the follow-up period, 24 sessions of acupuncture treatments will be compensated for free according to the subject's wishes.

**Table 1 T1:** Location of non-acupoints in minimal acupuncture group.

**Non-acupoints**	**Location**
NA1	In the outside of the forearm, 1 cm outside the midpoint of the line between Yangchi (TE4) and Waiguan (SI4)
NA2	In the outside of the forearm, 1 cm outside the midpoint of the line between Shousanli (LI10) and Quchi (LI11).
NA3	In the abdomen, 1 cm outside the midpoint of the line between Daheng (SP15) and Fushe (SP13)
NA4	In the outside of the calf, 1 cm below the midpoint of the line between Zusanli (ST36) and Yanglingquan (GB34)
NA5	In the back of the foot, the midpoint of the line between Qiuxu (GB40) and Jiexi (ST41)

*NA, non-acupoints*.

### Outcomes

Figure 2 summarizes the outcomes and time points of data collection during the trial.

**Figure 2 F2:**
[figure not shown]
SPIRIT figure.

#### Primary Outcome Measurement

The primary outcome will measure changes in the HAMD-17 scores between baseline and 8 weeks after randomization. The Hamilton Depression scale (22), developed by [name] in 1960, is a widely used depression scale. It includes cognitive impairment, block, despair, anxiety/somatization, sleep disorder, weight, and diurnal changes. It is mainly used to evaluate the severity of depressive symptoms in adult patients with depression and the curative effect before and after clinical trials. The higher the score, the more serious the degree of depression.

#### Secondary Outcomes

##### HAMD-17 at Other Timepoints

The primary outcome measurement is the HAMD-17 at week 8 after randomization; however, it will also be used at weeks 4 and 20 after randomization.

#### Symptom Assessment

Compared with the baseline period, the changes in PHQ-9, SF-12v2, and GAD-7 scores and the proportion of people who developed moderate depression (HAMD-17>17 or PHQ-9>10) at weeks 4, 8, and 20 will be measured. The PHQ-9 is a self-reporting tool to evaluate 9 depressive symptoms according to the DSM-IV depression criteria. It has a total of 9 items, each with a score of 4 (0–3), leading to a total score of 0–27. This score can be used to describe the patient's symptoms (23). The Chinese version of the PHQ-9 has also proven its reliability and validity (24, 25). The SF-12v2 is a scale widely used to measure quality of life (26). At present, the second edition is widely used and mainly evaluates the two general dimensions of physical health (PCS) and mental health (MCS). The higher the score, the better the health-related quality of life. The GAD-7 is a self-reporting tool that assesses anxiety symptoms and aims to measure the frequency of anxiety symptoms over the past two weeks (27). Scores of 5, 10, and 15 points represent thresholds for mild, moderate, and severe anxiety symptoms, respectively.

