**Methods:**

This will be a prospective, randomized, controlled, and double-blind study of 64 patients with subthreshold depression. They will be randomly assigned as verum or minimal acupuncture group members. Patients in the verum acupuncture group will receive acupuncture at the acupoints, and those in the minimal acupuncture group will receive minimal acupuncture at non-acupoints. The interventions will be delivered over an 8-week period. The primary outcome measure will be the Hamilton Depression Scale-17 (HAMD-17). The secondary outcome measures will be the 9-item Patient Health Questionnaire (PHQ-9), 7-item Generalized Anxiety Disorder (GAD-7), and SF-12v2 Health Survey. The assessments will occur at baseline, 4 weeks, 8 weeks, and during a follow-up period.

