### Inclusion Criteria

Participants will be included if they meet the following criteria:

The Mini International Neuropsychiatric Interview (MINI version 5.0) will be used to identify subthreshold depression patients who have depressive symptoms but do not meet the major depression disorder criteria according to the Diagnostic and Statistical Manual of Mental Disorders (Fifth Edition) (DSM-V);Aged between 18 and 60 years;The score of HAMD-17:7 ≤ HAMD <17;No treatment related to depression has been received in the past 2 weeks;Antibiotics, probiotics, yogurt, and other fermented dairy products were not taken before random sampling;Voluntarily participating in this trial with a written informed consent form.

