### Exclusion Criteria

Participants with the following conditions will be excluded:

Meeting the criteria for major depressive disorder, bipolar disorder, or psychotic disorder according to DSM-V;Patients with severe liver and kidney damage, severe arrhythmia, or cardiac insufficiency;Pregnant women;Depression caused by psychoactive, non-addictive substances, or brain diseases;Patients have suicidal attempt or behavior;Patients who cannot tolerate acupuncture;Patients who are difficult to communicate with or do not cooperate with the researcher;Other situations determined by the researchers to be unsuitable for observation.

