### Statistical Analyses

R 4.0.5 software will be used for statistical analysis by an independent statistician who will not participate in the study. Two-tailed *p*-values < 0.05 will be considered statistically significant. Normally distributed continuous variables will be presented using the means and standard deviation, and non-normal variables will be presented as the medians and interquartile range. All efficacy analyses will be performed using the intent-to-treat (ITT). Missing data will be replaced according to the principle of the last observation carried forward method (28). The per-protocol (PP) population will be analyzed to determine the consistency of the results. The data before and after treatment in each group will be compared based on a paired *t* test or Wilcoxon signed-rank test, and the comparison between groups will be performed using an independent sample *t* test or Mann–Whitney *U* test. Categorical variables will be analyzed using the χ^2^ test or Fisher's exact test. For comparisons of the primary outcomes across the groups, we will use analysis of covariance with the baseline HAMD-17 to adjust. A generalized linear mixed model will be used for repeated measures, setting group and time as fixed factors and patient as a random factor; the interaction effects of group^*^time will be included in the model.

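### The moderate-depression endpoint is worded as new onset, but its rule lets participants already above the PHQ-9 cut-off at entry count as events and leaves a HAMD-17 of exactly 17 unassigned

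*Protocol article*

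**What the plan says.** The endpoint stands in the Symptom Assessment section of the protocol article: "the proportion of people who developed moderate depression (HAMD-17>17 or PHQ-9>10) at weeks 4, 8, and 20 will be measured". The same sentence opens with a reference to baseline: "Compared with the baseline period, the changes in PHQ-9, SF-12v2, and GAD-7 scores". The section describes the PHQ-9 as a self-report scale, "leading to a total score of 0–27".

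The Inclusion Criteria limit one scale only: "The score of HAMD-17:7 ≤ HAMD <17". The other severity limits are diagnostic. The MINI interview is used to "identify subthreshold depression patients who have depressive symptoms but do not meet the major depression disorder criteria", and the Exclusion Criteria remove those "Meeting the criteria for major depressive disorder, bipolar disorder, or psychotic disorder according to DSM-V". Neither list mentions a PHQ-9 score.

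Under Statistical Analyses, "Categorical variables will be analyzed using the χ^2^ test or Fisher's exact test". Baseline adjustment is stated for the primary outcome only.

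**The concern.** A conversion endpoint needs a population that is free of the event at the start. The HAMD-17 entry ceiling secures this for the HAMD-17 limb, but nothing secures it for the PHQ-9 limb. Read literally, a participant whose PHQ-9 falls from 12 to 11 is recorded as having become moderately depressed.

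The two HAMD-17 limits also do not meet. Eligibility stops below 17 and the event starts above 17, so a participant who reaches exactly 17 has left the trial's own entry range without being counted.

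The Background and Discussion justify treatment largely by preventing progression to major depression, and this proportion is the listed outcome that counts conversions. With 32 participants per arm, a few misclassified people can change how it reads. Two analysts could also report different proportions from the same data, depending on whether they followed the verb or the parenthesis.

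**Working it through.** **The plan's own figures.** No figure is attached to this endpoint. The only stated calculation is for the primary outcome (Sample Size Estimation): difference 4.87, SDs 1.99 and 7.18, 27 per group, two-sided 0.05, unequal-variance *t* test.
- Standard error = √[(1.99² + 7.18²)/27] = 1.434
- Noncentrality = 4.87/1.434 = 3.396, with Satterthwaite df = 29.97
- Power = 90.75%, as stated
- 27/(1 − 0.15) = 31.8, so 32 per group and 64 in total, as stated

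None of this depends on the moderate-depression endpoint.

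**Entry range against event range (integer scores).**

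| Scale | Allowed at entry | Event | Consequence |
|---|---|---|---|
| HAMD-17 | 7–16 | 18 and above | 17 is neither; any event is a rise of at least 2 points |
| PHQ-9 | 0–27 (no limit) | 11–27 | every event score is also allowed at entry |

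Because the limbs are joined by *or*, a HAMD-17 of 17 is missed only when PHQ-9 is 10 or lower.

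**Size of the PHQ-9 problem.** Let *q* be the share above 10 at entry and *r* the share of those still above 10 at the visit. The article gives neither, so I assume *q* = 0.20–0.40 and *r* = 0.30–0.70. The carried-over share is *q* × *r*:
- Low: 0.20 × 0.30 = 0.06, and 0.06 × 32 = 1.9 per arm
- High: 0.40 × 0.70 = 0.28, and 0.28 × 32 = 9.0 per arm

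**Chance imbalance.** The SD of the arm difference in the *baseline* share is √[2*q*(1 − *q*)/32] = 0.10 at *q* = 0.20 and 0.122 at *q* = 0.40. Only those who persist reach the endpoint, so an imbalance of one SD passes through as 0.10 × 0.30 = 0.03 to 0.122 × 0.70 = 0.086, roughly 3 to 9 percentage points.

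**Noise and dilution.** Suppose persistence is the same in both arms and, for simplicity, ignore HAMD-17 events in those above 10 at entry. The counted proportion in an arm is then *qr* + (1 − *q*)*c*, where *c* is that arm's conversion rate among those truly at risk. The arm difference is (1 − *q*)(*c*₁ − *c*₂), so the true difference is multiplied by 0.80 to 0.60. The carried-over events add variance. With an assumed *c* of 8%:
- Low: new events 0.80 × 0.08 = 0.064; all counted events 0.124. The SD of the arm difference, √[2*p*(1 − *p*)/32], rises from 0.061 to 0.082.
- High: new events 0.60 × 0.08 = 0.048; all counted events 0.328. The SD rises from 0.053 to 0.117.

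**The case against.** The strongest reply is that the text already means new cases. It uses the verb *developed* and opens with a comparison to baseline, and someone above 10 throughout has developed nothing. A journal article may leave the handling of such participants to the full protocol or analysis plan. The first half stands: the article nowhere says that prevalent cases are to be counted, so this is an unenforced intention and not a stated rule to count them. The second half does not dispose of the point. The article gives an operational rule, with cut-offs and visits, and that rule taken by itself admits prevalent cases.

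A second reply is that excluding major depression makes a high PHQ-9 unlikely at entry, since the items follow the DSM criteria. That has force for very high scores. But even supposing the exclusion kept every entrant below five items scored 2 or 3 (an assumption), the total could reach 4 × 3 + 5 × 1 = 17, so scores of 11 to 17 remain open.

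Third, an event limit need not be the exact complement of an eligibility limit, and the gap is a single score that matters only when PHQ-9 is 10 or lower. That is fair. It is a small inconsistency, worth settling because the definition is being reworded anyway.

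Finally, the imbalance is chance variation under randomization, which the planned test allows for. This stands: the effect is noise and dilution, not systematic bias.

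**Conclusion.** The point holds as a defect of definition in a secondary outcome. It should be corrected, but the primary outcome and the sample size of 64 are untouched.

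Two facts rest on the text alone: the PHQ-9 limb can be met at baseline, and a HAMD-17 of 17 falls between the two limits. The size does not rest on the text. About 2 to 9 carried-over events of 32 per arm follows only from the assumed 20–40% above the cut-off and 30–70% persistence; no baseline PHQ-9 distribution is given.

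A reader might infer more than this supports:
- *That the endpoint fails to measure progression.* It does not fail altogether. Everyone starts at a HAMD-17 of 16 or lower, so the HAMD-17 limb records real worsening. Change in HAMD-17 and PHQ-9 at the same visits also shows deterioration.
- *That carried-over cases swamp true conversions.* They may outnumber them under some assumptions, but the documents fix neither number.
- *That a 10 to 12 point SD applies to the endpoint.* It describes the baseline share; the part passed on to the endpoint is smaller.

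**What to change.** Define the event at each visit as a new crossing after baseline: HAMD-17 of 17 or more, or PHQ-9 above 10 in a participant whose baseline PHQ-9 was 10 or lower. Participants above 10 at baseline then remain at risk through the HAMD-17 limb only. Setting the HAMD-17 limb at 17 or more reconciles it with the entry limit and leaves no score between them. Reporting each limb with its own number at risk would make the result easy to read.

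Keep the planned χ² or Fisher test. The defect does not call for a covariate-adjusted model, which would be fragile with few events among 64 people.

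No new data are needed, since "The assessments will occur at baseline, 4 weeks, 8 weeks, and during a follow-up period". The cost is fewer counted events and a smaller group at risk for the PHQ-9 limb: on the assumed 20–40% above the cut-off at entry, 32 × 0.80 = 25.6 to 32 × 0.60 = 19.2, or about 19 to 26 per arm.

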#### Evaluation of Acupuncture Tolerance

**A** visual analog scale (VAS) will be used to evaluate the discomfort of acupuncture after the first and last treatment. We will use a three-point method to evaluate acupuncture receptivity, which is unacceptable (0 points), acceptable (1 point), or easy to accept (2 points). Those who cannot accept acupuncture will write down the reasons clearly.

#### Evaluation of Acupuncture Expectation

Before the first treatment, we will use the acupuncture expectancy scale to evaluate the expectation of acupuncture in the subjects. The higher the score, the higher the expectation for the efficacy of acupuncture.

#### Blind Success Rate Evaluation

The percentage of patients who choose acupuncture will be compared between the two groups at the end of the last treatment.

#### Adverse Events

The contents include broken needles, missing needles, dizziness after acupuncture, unbearable acupuncture pain (VAS ≥ 8), severe post-acupuncture pain lasting more than 2 h (VAS ≥ 4), local hematoma, infection, or abscess. Other unforeseen adverse events will be recorded at all trial periods.

#### Exploratory Outcomes

Patient blood samples and feces will be collected at week 0 and week 8 after randomization and will be used to establish a biological sample bank, which may help to promote the research program and explore the therapeutic mechanism of acupuncture intervention in subthreshold depression.

Normally distributed continuous variables are presented using the means and standard deviation.

### Data Collection

All participant data will be recorded on the original case report forms (CRFs). To ensure the accuracy of the data, the data will be entered into Excel 365 by two independent data entry clerks. All paper data related to the trial will be saved, and electronic documents will be stored in a password protected computer. All research documents, including paper and electronic documents, will be preserved for at least 5 years after publication. If readers have any questions about the data we publish, they can contact the first author or corresponding author for the original data. Private information, such as the patient's name, age, and phone number, will be protected and will never be disclosed to anyone. Feces and blood samples will be collected in strict accordance with standardized procedures and stored in a −80°C freezer to establish a biological sample bank.

### Statistical Analyses

R 4.0.5 software will be used for statistical analysis by an independent statistician who will not participate in the study. Two-tailed *p*-values < 0.05 will be considered statistically significant. Normally distributed continuous variables will be presented using the means and standard deviation, and non-normal variables will be presented as the medians and interquartile range. All efficacy analyses will be performed using the intent-to-treat (ITT). Missing data will be replaced according to the principle of the last observation carried forward method (28). The per-protocol (PP) population will be analyzed to determine the consistency of the results. The data before and after treatment in each group will be compared based on a paired *t* test or Wilcoxon signed-rank test, and the comparison between groups will be performed using an independent sample *t* test or Mann–Whitney *U* test. Categorical variables will be analyzed using the χ^2^ test or Fisher's exact test. For comparisons of the primary outcomes across the groups, we will use analysis of covariance with the baseline HAMD-17 to adjust. A generalized linear mixed model will be used for repeated measures, setting group and time as fixed factors and patient as a random factor; the interaction effects of group^*^time will be included in the model.

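### Last observation carried forward in the primary week-8 HAMD-17 analysis shrinks any true effect and, if dropout differs by arm, can create a false one; the mixed model already planned needs no such filling

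*Protocol article*

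**What the plan says.** The primary endpoint is set under Primary Outcome Measurement: "The primary outcome will measure changes in the HAMD-17 scores between baseline and 8 weeks after randomization". HAMD-17 has one visit between these two time points and one after treatment: "it will also be used at weeks 4 and 20 after randomization". Treatment lasts eight weeks ("The interventions will be delivered over an 8-week period"), so week 20 lies 12 weeks after it ends.

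The Statistical Analyses section then fixes five things:

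- Population: "All efficacy analyses will be performed using the intent-to-treat (ITT").
- Missing data: "Missing data will be replaced according to the principle of the last observation carried forward method (28").
- Consistency check: "The per-protocol (PP) population will be analyzed to determine the consistency of the results".
- Primary test: "For comparisons of the primary outcomes across the groups, we will use analysis of covariance with the baseline HAMD-17 to adjust".
- Repeated measures: "A generalized linear mixed model will be used for repeated measures, setting group and time as fixed factors and patient as a random factor", with the group-by-time interaction included.

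The carry-forward rule is stated without exception. The section does not say whether the mixed model is fitted to filled or to observed data. Sample Size Estimation assumes 15% dropout, with 32 participants per group.

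**The concern.** Carrying the last observation forward (LOCF) assumes that a participant's score stays where it was at the last visit. With HAMD-17 visits at baseline, week 4 and week 8, someone who leaves before week 4 enters the primary analysis with zero change. Someone who leaves between weeks 4 and 8 enters with the week-4 change.

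Scores can be expected to fall in both arms. Both receive needling for eight weeks, and the Background itself says that placebo can reduce depressive symptoms. Two consequences follow. A real difference is diluted, because dropouts contribute only part of it. And any difference between arms in how many leave, or when, is turned into an apparent treatment difference. The trial asks whether acupuncture does more than placebo, so a between-arm artefact goes to its main conclusion.

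At week 20, a missing score is replaced by one from week 8 or earlier. For those participants, persistence of the effect is assumed, not measured.

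**Working it through.** **The plan's own figures.** Inputs from Sample Size Estimation: difference 4.87, SDs 1.99 and 7.18, 27 per group, two-sided alpha 0.05, unequal-variance t test.

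- Variance of the difference: (1.99² + 7.18²)/27 = (3.96 + 51.55)/27 = 2.056, so SE = 1.434.
- Noncentrality: 4.87/1.434 = 3.40, with Satterthwaite df 29.97. Power is 90.75%, as stated.
- Dropout: 27/0.85 = 31.8, rounded up to 32 per arm and 64 in total, as stated. Planned dropout is 0.15 × 32 = 4.8, about 5 per arm.

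The sample size arithmetic is sound. The issue is how those 5 per arm are analysed.

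**Equal dropout, true effect 4.87.** Let d be the dropout share and f the fraction of the week-8 effect present in the carried value. Then LOCF difference = (1 − d) × 4.87 + d × f × 4.87.

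- All carried from baseline (f = 0): 0.85 × 4.87 = 4.14.
- All carried from week 4, half the effect reached (f = 0.5): 4.14 + 0.15 × 2.435 = 4.50.
- Dropout split evenly before and after week 4: 4.14 + 0.075 × 2.435 = 4.32.

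Simulated baseline-adjusted ANCOVA with the even split gives 4.3 to 4.4, and 95% confidence interval coverage of 92 to 93%. ANCOVA on observed scores gives 4.85 to 4.88 with 95% coverage.

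**No true effect, unequal dropout.** The article gives no expected trajectories, so these are assumed: means 12, 9.5 and 7.5 at weeks 0, 4 and 8 in both arms; SDs 3, 4 and 4; correlations 0.5 to 0.65; 32 per arm; dropout unrelated to score and split evenly before and after week 4. Each dropout before week 4 is scored 12 − 7.5 = 4.5 points too high on average, and each later one 9.5 − 7.5 = 2 points too high. Negative values favour verum.

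| Dropout, verum / minimal | Excess per period in minimal arm | Expected false difference | Simulated LOCF difference | Type I error, LOCF |
|---|---|---|---|---|
| 15% / 15% | 0 | 0 | 0.00 | 5.0% |
| 10% / 20% | 5 points | −(0.05 × 4.5 + 0.05 × 2) = −0.325 | −0.33 | 6.5% |
| 10% / 25% | 7.5 points | −(0.075 × 4.5 + 0.075 × 2) = −0.49 | −0.50 | 8.2% |

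On observed scores, type I error in the two unequal rows is about 5%. Swapping the arms reverses the sign.

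A harsher set of assumptions shows the sensitivity: a mean improvement of 7 points in both arms, half of it by week 4, common SD 5.27, correlation 0.6, dropout 5% versus 25%. The expected false difference is 0.20 × (0.5 × 7 + 0.5 × 3.5) = 1.05 points. Simulation gives 1.07 and a type I error of about 15%.

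**Week 20.** If 30% of the benefit is lost after treatment (assumed), the true difference is 0.7 × 4.87 = 3.41. LOCF gives 3.08 to 3.43 across the dropout patterns tried, and a false 0.27 under no effect with 5% versus 25% dropout. Other post-treatment courses would give other values.

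**The case against.** **Nothing in the article predicts unequal dropout.** It plans a single 15% rate, and with no effect and equal patterns LOCF is unbiased and holds its level. This stands: the false-positive risk is conditional. Equal dropout cannot be presumed either, since the arms differ in needle sensation and the acupuncturists are unblinded. The dilution of a true effect needs no imbalance at all.

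**The power loss is small at the plan's own effect.** This also stands. At 4.87 points and 15% dropout, LOCF costs about 1 to 4 points of power (for example 92% against 96% with the plan's SDs). Larger losses appear only for smaller effects: with a true 2.5 points under the assumed trajectories, 64% against 73%. A reader might infer that the rule leaves the trial underpowered; the plan's own figures do not support that. The harm at 4.87 is an estimate about 11% too small.

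**There are partial safeguards.** Elimination and Withdrawal Criteria lists dropouts, so the per-protocol set probably resembles a completers' analysis and might reveal a distortion. Quality Control plans retention efforts and an analysis of dropout reasons. These help, but none tests the missing-data assumption or changes the primary estimate.

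**This is described as a pilot and a preliminary exploratory study.** That lowers the stakes, but the article still states that it aims to assess efficacy, and the result is to decide whether multicentre research follows.

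**Conclusion.** The point holds in conditional form. LOCF governs the primary week-8 comparison. It pulls a true 4.87 points to about 4.3 to 4.4 at the planned dropout if half the effect is present by week 4 (4.14 to 4.50 across carry-forward timings). When both arms improve and dropout differs in amount or timing, it produces a false difference in either direction: about 0.33 points with 6.5% type I error at 10% versus 20%, and about 0.50 with 8.2% at 10% versus 25%. These sizes rest on the assumed trajectories and on dropout unrelated to score.

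Three stronger readings are tempting but not supported:

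- *LOCF biases the comparison in every case.* With no effect and equal dropout patterns the bias is zero and the type I error stays near 5%.
- *LOCF separately understates uncertainty.* With a true effect of 4.87, simulated SEs were about 4 to 9% smaller than without filling, but they matched the actual spread of the LOCF estimates (for example 1.09 against 1.09 to 1.10). The lost coverage at week 8 comes mainly from the shift in the estimate.
- *LOCF overstates lasting benefit at week 20.* Persistence is assumed for participants with missing scores, but size and direction depend on unknown post-treatment change. Under the one course tried, the bias was 0 to 0.3 points.

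Nor does the article say that filled values enter the mixed model; it leaves this open.

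**What to change.** In Statistical Analyses, state that LOCF applies neither to the primary analysis nor to the mixed model. Take the week-8 group contrast from the repeated-measures mixed model already planned, fitted to the observed HAMD-17 scores of all randomised participants, with baseline HAMD-17 as a covariate and group, time and their interaction as fixed effects. Such a model uses incomplete records and is valid if data are missing at random. Because that assumption cannot be verified, name one sensitivity analysis that departs from it. Keep LOCF, if wanted, only as a labelled sensitivity analysis.

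The cost is a few sentences and a slightly more complex primary model; no new participants, visits or data are needed. Trial Status gives a start in July 2021, so the change needs a dated amendment, notified to the Ethics Committee and made before unblinding.

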### Sample Size Estimation

This pilot study aims to assess the efficacy of acupuncture for subthreshold depression as well as the feasibility of a further large clinical trial. The HAMD-17 was used as the main effect indicator to calculate the required sample size. According to relevant published literature (19, 20), the difference in HAMD-17 scores between the acupuncture and placebo groups was 4.87, and the standard deviation was 1.99 in the acupuncture group and 7.18 in the placebo group. Group sample sizes of 27 and 27 achieve 90.75% power to reject the null hypothesis of equal means and with a significance level (alpha) of 0.050 using a two-sided two-sample unequal-variance *t* test by PASS 15 software. Assuming a dropout rate of 15%, 64 participants are necessary, with 32 participants in each group.

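### Baseline adjustment is specified only for the primary outcome; the continuous secondary outcomes have an uncovaried test and a mixed model without a baseline term, and neither is named as governing.

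*Protocol article*

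**What the plan says.** Three statements in Statistical Analyses bear on the continuous outcomes.

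- General rule: "the comparison between groups will be performed using an independent sample" t test or a Mann–Whitney U test. No covariate is named.
- Primary outcome: "For comparisons of the primary outcomes across the groups, we will use analysis of covariance with the baseline HAMD-17 to adjust".
- Repeated measures: a generalized linear mixed model with group, time and group×time as fixed terms and patient as a random term. It is not tied to a particular outcome, no baseline covariate is listed, and the text does not say whether baseline is one of the time levels.

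The outcome sections make HAMD-17 at weeks 4 and 20 secondary. For the other scales, Symptom Assessment gives the secondary measures at weeks 4, 8 and 20 as "Compared with the baseline period, the changes in PHQ-9, SF-12v2, and GAD-7 scores". The abstract's assessment schedule includes baseline.

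**The concern.** The sponsor accepts baseline adjustment for HAMD-17 at week 8 but, on a plain reading, does not extend it to the same scale at weeks 4 and 20 or to the other scales. Three things follow.

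- **Precision.** A comparison of change scores, or of follow-up scores, without a baseline covariate has at least as large a variance as ANCOVA, and usually a larger one. A change score also tends to over-correct a chance baseline difference, and a raw follow-up score does not correct it at all. With 32 randomized per arm, such differences are to be expected.
- **Quantity tested.** A t test addresses a difference in means and a Mann–Whitney test addresses rank ordering. If both are used, two visits of one scale may be reported on different quantities.
- **Which result counts.** A t test, a rank test and a mixed-model contrast can all be applied to the same secondary outcome, and none is named as the governing analysis.

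**Working it through.** **1. The plan's own figure.** Sample Size Estimation supplies the inputs: "the difference in HAMD-17 scores between the acupuncture and placebo groups was 4.87"; "the standard deviation was 1.99 in the acupuncture group and 7.18 in the placebo group"; 27 per arm; alpha 0.05, two-sided, unequal-variance t test.

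- Variance of the difference: 1.99²/27 + 7.18²/27 = 0.147 + 1.909 = 2.056, so SE = 1.434.
- Noncentrality: 4.87/1.434 = 3.40. Welch–Satterthwaite df = 29.97.
- Power from the noncentral t distribution: 90.75%, as stated.
- Dropout: 27/(1 − 0.15) = 31.8, rounded up to 32 per arm and 64 in total, as stated.

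The stated figures reproduce. They concern HAMD-17 only, and no figure is given for the other scales.

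**2. Precision formulas.** Let s0 and s1 be the baseline and follow-up SDs and r their correlation. For a given n, the variance of the group difference is proportional to:

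- follow-up score alone: s1²
- change score: s0² + s1² − 2·r·s0·s1
- ANCOVA: s1²(1 − r²)

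The change-score term minus the ANCOVA term equals (s0 − r·s1)², which is never negative. Apart from the cost of one degree of freedom, ANCOVA is therefore never less precise.

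**3. Equal SDs (assumption).** The ratio of ANCOVA to change score is (1 − r²)/(2(1 − r)) = (1 + r)/2. The ratio of ANCOVA to follow-up score is 1 − r². The documents give no r, so 0.3 to 0.7 is assumed.

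| r | ANCOVA / change | n per arm on change scores matching 27 with ANCOVA | ANCOVA / follow-up | n per arm on follow-up scores matching 27 with ANCOVA |
|---|---|---|---|---|
| 0.3 | 0.65 | 27/0.65 ≈ 42 | 0.91 | 27/0.91 ≈ 30 |
| 0.5 | 0.75 | 27/0.75 = 36 | 0.75 | 27/0.75 = 36 |
| 0.7 | 0.85 | 27/0.85 ≈ 32 | 0.51 | 27/0.51 ≈ 53 |

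**4. The same in power.** Assume a standardized difference of 0.5 in follow-up SD units and 27 per arm. Noncentrality is 0.5·√(27/2) = 1.84 for the follow-up t test. It is divided by √(2(1 − r)) for change scores and by √(1 − r²) for ANCOVA.

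| r | follow-up t | change-score t | ANCOVA |
|---|---|---|---|
| 0.3 | 44% | 33% | 47% |
| 0.5 | 44% | 44% | 55% |
| 0.7 | 44% | 64% | 71% |

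**5. Unequal SDs, HAMD-17.** Eligibility restricts baseline HAMD-17 to 7 to 16. A uniform spread over those ten scores, taken for illustration, has SD √((10² − 1)/12) = 2.87. The root mean square of the two planning SDs is √((1.99² + 7.18²)/2) = 5.27; using it as the follow-up SD is a second assumption. Here s1²(1 − r²)/(s0² + s1² − 2·r·s0·s1) gives:

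- r = 0.3: 25.26/26.93 = 0.938, a reduction of about 6%
- r = 0.5: 20.82/20.87 = 0.997, about 0.3%
- r = 0.7: 14.16/14.82 = 0.955, about 4.5%

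**6. Switching tests.** The protocol states no selection rule, so a Shapiro–Wilk pretest was assumed in 20,000 simulated null trials of 27 per arm. With equal normal SDs, type I error was 4.8%. With normal data at SDs 1.99 and 7.18 it was 6.1%, against 5.4% for the t test alone and 7.1% for Mann–Whitney alone. About 10% of these normal-data trials went to the rank test.

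**The case against.** The strongest reply is that this is one paragraph of a journal article. Covariates for secondary models and rules for choosing a test are commonly left to an analysis plan, change-score and rank comparisons are conventional and valid, and the study calls itself a pilot. It is fair that silence on a selection rule is no fault in itself. What stands is what the text does state: an uncovaried comparison as the general rule, covariate adjustment for the primary outcome only, and a model whose listed terms omit baseline.

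A reader might infer four stronger things, which the documents do not support.

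- **That secondary outcomes receive only an unadjusted test.** The mixed model is not restricted to one outcome. If baseline is a time level, its group×time contrast removes baseline much as a change score does, though less efficiently than ANCOVA.
- **That the test will be picked after seeing the data.** The normal/non-normal wording governs how variables are presented. Data-driven choice is a natural inference but is not stated, and the simulated effect on type I error is small.
- **That HAMD-17 at weeks 4 and 20 is a change score tested without adjustment.** The section on other time points says only that the scale is used then. The plural in the ANCOVA sentence could be stretched to cover those visits, although the protocol lists them as secondary.
- **That a 15% to 35% variance reduction applies throughout.** It needs equal baseline and follow-up SDs. Step 5 of the working shows it can almost vanish for HAMD-17.

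**Conclusion.** The point holds for secondary outcomes. The article states baseline adjustment for the primary outcome alone, offers two tests with different targets plus a mixed model without a baseline covariate, and does not rank them. With equal SDs, the variance saved by ANCOVA against change scores is 35%, 25% or 15% at r = 0.3, 0.5 or 0.7. For HAMD-17 under a restricted baseline it may be from near zero to about 6%. Neither r nor the SDs of PHQ-9, GAD-7 and SF-12v2 are in the documents, so the actual size cannot be fixed; its direction can. The larger practical gain may be a single named analysis with one estimand at every visit. The stated power, the sample size and the primary analysis are unaffected.

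**What to change.** Name the repeated-measures model already planned as the governing analysis for every continuous secondary outcome. Use post-baseline visits as the time levels, and include group, week, group×week and the scale's own baseline as a covariate. Report adjusted mean differences with 95% confidence intervals at weeks 4, 8 and 20. Week 8 is already covered by the primary ANCOVA for HAMD-17, so state that the primary analysis is unchanged. Keep the Mann–Whitney test only as a prespecified sensitivity analysis.

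The cost is wording in the analysis section. The baselines are already collected, and no patients, visits or measurements are added.
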